## Methods

### Evaluation Methodology and Measurement Plan

In the Text4Hope program, individuals self-subscribe to receive daily supportive text messages for 3 months by texting “COVID19HOPE” to [name]. The messages are aligned with a cognitive behavioral framework, with content written by mental health therapists as well as our research team members (authors MH and [name]). The following is an example of the messages sent: “When bad things happen that we can’t control, we often focus on the things we can’t change. Focus on what you can control; what you can do to help yourself (or someone else) today” [29]. The messages are preprogrammed into an online software that delivers messages at 9 AM each morning. At the onset of the first message, respondents are welcomed to the service and are invited to complete an online baseline survey capturing demographic information; COVID-19–related self-isolation/quarantine information; and responses on the Generalized Anxiety Disorder-7 (GAD-7) scale [30], Perceived Stress Scale [31], and the Patient Health Questionnaire-9 (PHQ-9) [32]. Survey questions were programmed into SelectSurvey.net, an online survey tool operated by the Alberta Health Services Evaluation Services Team. No incentives are offered to respondents. Participation in the program is entirely voluntary, and completion of the survey was not a prerequisite requirement to receive supportive text messages. Subscribers may opt out at any time by texting “STOP” to [name]. Survey responses will be stored within our regional health system (Alberta Health Services) Select Survey account, and data will be exported, stored, and maintained by the Research and Evaluation team within our health region. The supportive SMS text messaging project subscriber recruitment plan was based on the success of a Text4Mood program in Alberta that was launched in response to the Fort McMurray wildfire disaster in 2016. Text4Hope has been the subject of a wide-exposure communications campaign (TV, radio, internet, and print media), including the local provincial mental health foundation, the single provincial government health care provider Alberta Health Services (AHS). Additionally, Text4Hope was the subject of a specific COVID-19 mental health support media release by the Provincial Chief Medical Officer [33]. Ethics approval has been granted by the University of Alberta Health Research Ethics Board (Pro00086163).

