### Sample Size Considerations

Based on previous experience using the technology, (ie, >10,000 recipients within 6 months), we expect about 300,000 Canadians to subscribe to the Text4Hope program over the next 6 months. Based on a response rate of 21.7% for our prior Text4Mood survey [27], we anticipate around 20,000 responses to the Text4Hope surveys per 100,000 subscribers.

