We will evaluate the efficacy of Text4Hope with the reductions of perceived stress, anxiety, and depression at 6 weeks and 12 weeks. Data analysis will include the standard use of parametric and nonparametric techniques (eg, within-subject general linear models), including multiple comparison Type 1 error corrections. Power analysis with effect sizes based on [name] group research publications [26-28,36,37] indicates a sufficient effect size for the expected Text4Hope program subscriber sample size. As the sample size for the data set generated from this project will be large, in addition to the conventional statistics used in these projects, we plan to adopt a “big data” analysis approach to examine data-driven patterns. Using machine learning and data mining methods, we expect to capture the most powerful window on differences and high-order sets of potential interactions. With our program targeting 300,000 Canadians to self-subscribe, with an expected 60,000 completing the survey, we are confident that this project has adequate power for our basic cross-sectional approach. We will develop predictive models using baseline measurements (features) and machine learning algorithms (eg, the least absolute shrinkage and selection operator [LASSO], support vector regression [SVR], and random forest regression, etc [38-40]) to predict the efficacy of our intervention at 6 and 12 weeks, as measured by the change in assessment scores (eg, GAD-7, PHQ-9) compared to the baseline. We will perform a 10-fold cross-validation to evaluate the performance of the models. During cross-validation, the data will be randomly segmented into 10 folds, with each fold containing 10% of the data. For each iteration, 1 fold will be left out as the testing data and the remaining 9 will be the training data. Within each training session, another internal 10-fold cross-validation will be used to select the best features, algorithm, and corresponding hyperparameters as the model to be trained on this specific training session. The selected model in the training data will then be applied to the testing data. This procedure is crucial for predictive tools as the data being tested has never been seen in any way by the model. The performance of the models will be evaluated using the Pearson correlation between the predicted and actual reduction of the outcome measures.

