Limitations of this protocol include a lack of baseline data on stress, anxiety, and depression levels before self-isolation measures were implemented in Alberta; this was unavoidable as our study was initiated shortly after quarantine and self-isolation measures were introduced. Nonresponse bias may also affect the expected results, as program subscribers are a sample of the population, not the entire population of the province. Nonrespondents may differ in a systematic way compared to respondents. For example, they may differ in their baseline level of mental wellness, be more (or less) affected by the pandemic, or have limitations in literacy or English fluency. In view of the limitations noted above, any prevalence estimates must be interpreted with caution, and compared to the conventional baseline of subsequent conventional prevalence estimates. The authors also note that this protocol does not include a control group and this raises the question of specificity concerning hypothesis 3, which concerns reductions in perceived stress, anxiety, and depressive symptoms. Previous RCT work from this group has demonstrated the efficacy of supportive SMS text messaging in intervention groups, compared to control groups that did not receive supportive text messages; instead, the control group received the same survey requests as the intervention group in addition to a single text message every 2 weeks, thanking them for participating in the study [26,37]. Given the intention to provide support to the catchment population of this study and the prior evidence for efficacy, it would be unethical to include a control group in the current protocol. Nevertheless, prior studies did include subscriber satisfaction surveys, as does this protocol, and that measure will provide evidence for engagement of the subscribers with the program (simply put, if subscribers ignored the text messages, it is highly unlikely that there would be positive satisfaction survey results). In the current health implementation context of this protocol, the comparison of changes in outcome measures in relation to comparison with effect sizes from our prior work (together with an assessment of the degree of correspondence of subscriber satisfaction survey responses to changes in our outcome measures) will be a good indicator of subscriber engagement in the absence of a control condition. Despite these limitations and possible bias factors, our protocol will provide useful data about the mental health characteristics of individuals in the early stages of the COVID-19 pandemic. We expect that our results will represent an important initial source of information for government and health care planners in determining the nature and quality of services required to address mental health challenges arising during this pandemic, as well as future pandemics that employ self-isolation or quarantine measures. Specifically, planning for and implementing virtual care programs, including supportive SMS text messages, may be a fruitful approach to supporting isolated or quarantined individuals. In addition, we expect the supportive SMS text messaging intervention to have a positive effect on mental well-being and we will be able to measure this well within the expected sample size.

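### The one model named for the primary within-person change leaves out people without follow-up surveys, so selective response can bias the change that hypothesis 3 rests on; a mixed model on all linked surveys would be better

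*Protocol article*

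**What the plan says.** The Protocol article (Outcome Measures) defines the primary outcome as change from baseline at 6 and 12 weeks on the Perceived Stress Scale, GAD-7 and PHQ-9. Hypothesis 3 expects a reduction of at least 25% on each. The Results section describes the analysis as "the standard use of parametric and nonparametric techniques (eg, within-subject general linear models), including multiple comparison Type 1 error corrections". The within-subject general linear model is thus an example, but it is the only model named for the change itself. The machine-learning models in the same section serve prediction.

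On who answers, Sample Size Considerations states "we expect about 300,000 Canadians to subscribe to the Text4Hope program over the next 6 months" and "we anticipate around 20,000 responses to the Text4Hope surveys per 100,000 subscribers", the latter introduced by "Based on a response rate of 21.7% for our prior Text4Mood survey". The Results section plans "with an expected 60,000 completing the survey" and adds "we are confident that this project has adequate power for our basic cross-sectional approach". No response rate is given for week 6 or week 12, and no number of people with linked baseline and follow-up surveys.

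Evaluation Methodology and Measurement Plan makes the surveys voluntary, without incentive and not a condition for receiving messages. It adds "Subscribers may opt out at any time by texting" a stop word. The Discussion says "Nonrespondents may differ in a systematic way compared to respondents", with baseline mental wellness as one example. It spells out the consequence for prevalence estimates. For hypothesis 3 it names only the lack of a control group.

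**The concern.** A change score needs at least two surveys from the same person. A classical repeated-measures general linear model over three waves needs all three, and a separate comparison at each follow-up needs baseline plus that follow-up. In both cases the remaining baseline surveys go unused, although they hold the score and demographics that help to explain who comes back.

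If more distressed people are more likely to return, regression to the mean makes the remaining group appear to improve more than the whole. If they are less likely to return, the reverse happens. With no control arm, this error cannot cancel between groups. It goes straight into the figure compared with the 25% target and used when scale-up is considered. A large sample does not help: it narrows the interval around the wrong value.

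**Working it through.** **1. The plan's own figure.** 300,000 × 20,000/100,000 = 60,000, which matches the planned number of survey completers. The unrounded 21.7% would give 65,100; the article rounds down itself. The figure is a count of responders with no wave named, and the power statement attached to it is cross-sectional.

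**2. How many people carry the primary outcome.** Let c be the share of 60,000 baseline responders who answer a given follow-up, independently at each wave. The article does not give c, so a range is shown. Baseline plus one follow-up = 60,000 × c; all three waves = 60,000 × c².

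| c (assumed) | Baseline + one follow-up | All three waves |
|---|---|---|
| 10% | 6,000 | 600 |
| 20% | 12,000 | 2,400 |
| 30% | 18,000 | 5,400 |
| 50% | 30,000 | 15,000 |
| 100% | 60,000 | 60,000 |

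Precision is not the difficulty. At n = 2,400 the 95% half-width is 1.96/√2,400 = 0.04 SD of change.

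**3. Bias when response depends on baseline score.** Assumptions, none from the article: SD 6 at each wave, correlation 0.6 between baseline and week 12, true change −1.0 point, and logit(response) = −1.386 ± 0.3 × z at each follow-up, where z is the standardised baseline score (about 20% response).

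Given z, the expected change is −1.0 − (1 − 0.6) × 6 × z = −1.0 − 2.4z. The bias is therefore −2.4 × (mean z of those kept). Integrating over a normal z:

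| Group kept | Number | Mean z | Bias (points) | Estimated change | 95% half-width |
|---|---|---|---|---|---|
| Baseline + week 12 | about 12,260 | ±0.235 | ∓0.56 | −1.56 or −0.44 | 0.09 |
| All three waves | about 2,640 | ±0.464 | ∓1.11 | −2.11 or +0.11 | 0.20 |

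The upper sign applies when more distressed people respond more. In all four cases the interval excludes the true −1.0. Simulation under the same assumptions agrees within random error.

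Conditional on z, selection on z does no harm. A baseline-adjusted estimate averaged over all 60,000 baselines therefore returns −1.0. About 21,900 people have at least one follow-up.

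**4. Size against the target.** The bias does not depend on the assumed −1.0. At assumed baseline means of 10 to 20 points, a 25% reduction is 2.5 to 5 points. A bias of 1.11 points is then 44% to 22% of the target, and 0.56 points is 22% to 11%.

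**5. Bias when response depends on improvement itself.** A second simulation assumed no true change, 20% response at each follow-up and correlations of about 0.6 between adjacent waves and 0.5 between baseline and week 12. The false week-12 improvement, in baseline SDs, was:

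| Odds ratio of response per SD of improvement | Three-wave completers | Pairs |
|---|---|---|
| 1.0 | 0 | 0 |
| 1.25 | 0.29 | 0.17 |
| 1.5 | 0.50 | 0.31 |
| 2.0 | 0.80 | 0.51 |

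Conditioning on observed scores does not fully remove this kind of bias.

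**The case against.** The strongest reply is that the article fixes no method. The model is an example from an open list, and handling of missing surveys is normally left to a full protocol or analysis plan that is not shown. That is fair, and the absence of a missing-data section is not the point here. What can be improved is the choice of the one model that is named, since both of its usual forms leave out people without follow-up.

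Other replies also stand:

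- A reader might infer that only people who answer every wave would be analysed. The article does not say so, and pairwise comparisons would keep more people and roughly halve the bias in step 3. They do not remove it.
- A reader might infer that the plan expects 20% response at each wave. It does not. The 20% is rounded from one earlier survey of another program and is given without a wave. People who have answered once may well answer again.
- A reader might infer that the change would double or vanish. That rests on an assumed true change of −1.0 point and on counting three-wave completers only. Against a 25% reduction the same bias is a fraction of the effect.
- The Discussion does raise nonresponse in general terms. What it lacks is an explicit caution for the change estimate.
- The recovery of −1.0 in step 3 follows by construction, because response was made to depend on baseline alone. It shows what conditioning on observed data can do, not that all bias would go. Nor can any analysis of the surveys speak for subscribers who never complete one.

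**Conclusion.** The concern holds in limited form. The article's primary outcome needs linked repeat responders. The only model it names for that outcome discards people without follow-up, and its own account of the surveys makes selective response plausible. Under the assumptions in step 3, the week-12 change is off by about 1.1 points in three-wave completers and 0.6 points in pairs, with the direction set by who returns. The size in practice is unknown: it depends on follow-up response, the correlation between waves and the response mechanism, none of which is given. It would be close to zero if follow-up were nearly complete or unrelated to score and change. The problem is bias rather than power, and the documents do not show that the result will be badly wrong. The change is still worth making, because the better model uses data that the study will already have collected.

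**What to change.** - **Results section:** make the primary change analysis a linear mixed model, with wave as a categorical factor and unstructured covariance, fitted to every available linked survey. Include baseline-only responders and the demographics already collected.
- **Diagnostics:** report baseline scores of follow-up responders and nonresponders at each wave.
- **Sensitivity:** add an analysis for response that depends on unobserved change, for example a delta-shift with nonresponders unchanged from baseline. The mixed model covers only response that depends on observed data.
- **Discussion:** extend the nonresponse caution explicitly to hypothesis 3.
- **Weighting:** use the date of opting out in response weights only if opt-out records can be linked to surveys. The abstract calls the questionnaires anonymous, and the article shows no such link.

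The cost is revised wording and some programming, with slightly more complex analysis and reporting. Apart from the optional weighting, nothing beyond the planned surveys is needed, provided that a person's surveys can be linked across waves, which the primary outcome requires in any case.

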Due to the ongoing shifts in infection rates and public health measures over time, together with a shifting and unpredictable pattern of economic impacts, it will be important to include data on infection and death rates as well as the overall economic measures (including unemployment rates) associated with the baseline, 6-week, and 12-week measures. Such variables will be included in the machine learning analysis of the project data [41]. Including these variables will enable the model to account for variables that may influence expected rates of anxiety- and depression-related symptoms.

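### The prediction models use baseline scores to predict change from baseline on the same scales, so regression to the mean alone can produce the correlation that the plan would describe as predicting efficacy

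*Protocol article*

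**What the plan says.** All of the elements are in the protocol article.

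- **Features** (Results): "We will develop predictive models using baseline measurements (features) and machine learning algorithms". No feature list is given.
- **Baseline content** (Methods, Evaluation Methodology and Measurement Plan): besides demographic and isolation or quarantine items, the baseline survey collects "responses on the Generalized Anxiety Disorder-7 (GAD-7) scale [30], Perceived Stress Scale [31], and the Patient Health Questionnaire-9 (PHQ-9) [32".
- **Target and label** (Results): the models are meant "to predict the efficacy of our intervention at 6 and 12 weeks, as measured by the change in assessment scores", that is, change relative to baseline.
- **Performance measure** (Results): "The performance of the models will be evaluated using the Pearson correlation between the predicted and actual reduction of the outcome measures". No other measure is named.
- **Validation** (Results): ten outer folds, and within each training set "another internal 10-fold cross-validation will be used to select the best features, algorithm, and corresponding hyperparameters".
- **Extra covariates** (Results): infection, death and economic data. "Such variables will be included in the machine learning analysis of the project data".
- **Control group** (Discussion): the article acknowledges that "this protocol does not include a control group and this raises the question of specificity concerning hypothesis 3". It does not extend that caveat to the prediction models.

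**The concern.** The target is baseline minus follow-up. If the baseline score is also a feature, its measurement error and short-term fluctuation sit on both sides of the model. People who score unusually high on the day tend to fall back, and people who score unusually low tend to rise, whether or not the messages do anything. A learner picks this up, and the held-out data confirm it because the same coupling is present there. Nested cross-validation protects against overfitting, which is a different problem. The infection, death and economic variables leave the coupling in place.

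What is at stake is interpretation. A programme with no effect could yield a respectable cross-validated correlation, reported under a label that says efficacy was predicted. With no untreated group, individual benefit cannot be learned from these data at all.

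**Working it through.** The article states no model performance figure, so there is nothing to reproduce. The check asks what the planned metric returns when the programme does nothing.

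**Inputs.** Features, target and metric are as quoted. The article gives neither the baseline to follow-up correlation r nor the ratio k of follow-up SD to baseline SD. I assume r = 0.5 to 0.8 as the main range, with 0.4 and 0.9 as outer values, and k = 1, with 0.8 and 1.2 as sensitivity.

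**Closed form.** For baseline B, follow-up F, no effect and no differences in effect between people:

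corr(B, B − F) = (1 − rk) / √(1 + k² − 2rk)

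With k = 1 this is √((1 − r)/2). For example, r = 0.6 gives √0.20 = 0.447. With k = 1.2 and r = 0.8 it is (1 − 0.96)/√(2.44 − 1.92) = 0.04/0.721 = 0.055.

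| r | k = 0.8 | k = 1.0 | k = 1.2 |
|---|---|---|---|
| 0.4 | 0.680 | 0.548 | 0.427 |
| 0.5 | 0.655 | 0.500 | 0.359 |
| 0.6 | 0.631 | 0.447 | 0.280 |
| 0.7 | 0.610 | 0.387 | 0.184 |
| 0.8 | 0.600 | 0.316 | 0.055 |
| 0.9 | 0.626 | 0.224 | −0.151 |

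A fitted model would adopt the reversed slope in the last cell. The negative sign therefore describes the relation between baseline and reduction, not the score that the model would report.

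**Simulation on held-out folds.** 20,000 people; integer scores bounded at 0 to 21 (assumed mean 9, SD 5.5, before bounding); zero effect; linear model; single-level 10-fold cross-validation; ten pure-noise features throughout. The two other baseline scales are assumed to correlate 0.6 with the person's stable level. Mean change was about 0 in every run.

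| r | Own baseline score | Plus two other baseline scales | Difference | Other scales, own baseline left out |
|---|---|---|---|---|
| 0.4 | 0.547 | 0.614 | 0.067 | 0.006 |
| 0.5 | 0.502 | 0.585 | 0.083 | −0.005 |
| 0.6 | 0.451 | 0.548 | 0.097 | −0.015 |
| 0.7 | 0.392 | 0.494 | 0.102 | 0.002 |
| 0.8 | 0.322 | 0.419 | 0.097 | −0.006 |
| 0.9 | 0.222 | 0.310 | 0.088 | −0.002 |

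Three things follow.

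1. The held-out correlation matches the closed form, so cross-validation does not remove the artefact.
2. With the scale's own baseline left out, the correlation is about zero. The coupling is therefore the source.
3. The other scales predict nothing by themselves, but beside the own baseline they sharpen the estimate of each person's stable level and add 0.07 to 0.10. The gain over an own-baseline model is thus not zero under no effect either.

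**A real but uniform effect.** Lowering every follow-up score by 2.25 points, so that effects differ only through the scale floor, gave 0.54, 0.49, 0.45 and 0.39 for r = 0.5 to 0.8 with own baseline and noise. The correlation therefore separates poorly a programme that helps everyone equally from one that helps nobody.

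**Modelling the follow-up score instead.** With baseline as predictor, the no-effect correlation is r itself, 0.5 to 0.8 on the main range. That equals the figure for change at r = 0.5 and exceeds it above that.

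**The case against.** Predicting change from baseline covariates, the baseline score included, is legitimate, and regression to the mean is genuine out-of-sample predictability of change. The article defines its term operationally as change in scores, and the Discussion already concedes that there is no control group. A feature list and a comparator model are details that a condensed article may leave to a fuller document. The analysis is additional to the conventional statistics.

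Much of this stands, and it limits the point. The absence of a comparator is not in itself an error. That the baseline scores are features is a reading of two sections together, though the natural one, and the inner selection would be expected to keep them. What does not fall away is what the article itself fixes: the features, the target, a single metric, and a label that calls the result efficacy. The Discussion ties its caveat to hypothesis 3. The substitutes it offers, effect sizes from earlier work and satisfaction responses, do not separate regression to the mean from benefit in these models.

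A reader might also infer that the article treats zero as the no-effect benchmark, or that the models will pick out subscribers likely to benefit. It says neither: no threshold or null value is given, and no use of the models for selecting or targeting people is described.

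**Conclusion.** The point holds for the prediction analysis. Followed as written, it can return a held-out correlation of about 0.3 to 0.5 from the scale's own baseline score, or about 0.4 to 0.6 with all three scales, with no programme effect. These figures rest on equal SDs, an assumed r of 0.5 to 0.8 and, for the three-scale figure, the assumed correlations among scales.

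The mechanism is certain but the size is not. If the SD shrinks to 0.8 of its baseline value, the own-baseline figure is 0.60 to 0.66 over the same r. If it grows to 1.2 times, the figure falls from 0.36 to 0.06, and the relation between baseline and reduction turns negative at r = 0.9. A reader might conclude that the artefact must always be clearly positive; the article gives no r or SD ratio that would support this.

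A reader might also conclude that the primary result is undermined. This coupling does not touch it: the primary outcome is within-subject change at 6 and 12 weeks, and none of the four hypotheses depends on the models.

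**What to change.** In the machine learning text of the Results section:

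1. **Wording.** Where the article says the models are "to predict the efficacy of our intervention at 6 and 12 weeks, as measured by the change in assessment scores", state instead that they predict symptom change during the programme.
2. **Own-baseline comparator.** For each scale and time point, run a model with only that scale's baseline score through the same folds. Report its correlation beside that of each algorithm, with the increment.
3. **Three-scale comparator.** Do the same with all three baseline scale scores, because adding the other two raises the correlation even under no effect.
4. **If the follow-up score is modelled instead**, with baseline forced in, report only the increment over the baseline-only model. The raw correlation would be about r with no effect.
5. **Interpretation.** State that even the increment means better prediction of change and is not evidence of programme benefit.

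The cost is a few sentences and one or two simple models per scale and time point: at most 3 scales × 2 time points × 2 comparators = 12. The headline performance figure will look less favourable. No extra data are needed.

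### The prediction models are called models of efficacy, but their only score, correlation with raw change, can come from baseline severity and calendar effects alone

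*Protocol article*

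**What the plan says.** The Results section sets out the prediction analysis in some detail.

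- Features: "We will develop predictive models using baseline measurements (features) and machine learning algorithms". Under Methods, Evaluation Methodology and Measurement Plan, the baseline survey collects demographic and isolation or quarantine information and "responses on the Generalized Anxiety Disorder-7 (GAD-7) scale [30], Perceived Stress Scale [31], and the Patient Health Questionnaire-9 (PHQ-9) [32". The three scale scores are therefore baseline measurements.
- Target: the models are meant "to predict the efficacy of our intervention at 6 and 12 weeks, as measured by the change in assessment scores (eg, GAD-7, PHQ-9) compared to" baseline. The target is raw change, and it carries the name efficacy.
- Validation: "We will perform a 10-fold cross-validation to evaluate the performance of the models", with an inner 10-fold loop to choose features, algorithm and hyperparameters.
- Performance measure: "The performance of the models will be evaluated using the Pearson correlation between the predicted and actual reduction of the outcome measures". No other measure and no benchmark model is named.
- Further inputs: infection and death rates and economic indicators "associated with the baseline, 6-week, and 12-week measures. Such variables will be included in the machine learning analysis of the project data [41". The stated reason is to account for outside influences on symptoms.

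The Discussion says there is no control group and that this limits what can be concluded on hypothesis 3. It does not extend that limit to the prediction models.

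**The concern.** Two features of this set-up let the models look successful for reasons unrelated to the messages.

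First, the target is baseline minus follow-up, and baseline is among the features. Subscribers who join on a bad day tend to score lower later, so the baseline score predicts the reduction even if nothing was done. Nested cross-validation guards against overfitting, but this relationship is genuinely present in the population and will reappear in every held-out fold.

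Second, values observed at 6 and 12 weeks are not baseline measurements. A model that uses them explains change after the fact, and any movement of symptoms with the course of the pandemic is credited to its score.

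What is at stake is interpretation. The Discussion addresses practitioners and policy makers and foresees national scale-up if the program is effective. A cross-validated correlation of around 0.4, reported under the name efficacy and based on thousands of records, could be taken as evidence about whom the messages help. A single-arm study cannot supply that evidence.

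**Working it through.** **Inputs from the protocol.** Features, target, validation and performance measure are as quoted above. There is no control arm. The expected number of survey completers is 60,000, which follows from the plan's own rate: 300,000 × 20,000/100,000 = 60,000. The plan states no expected correlation or threshold for the models, so there is no such figure to reproduce.

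**Assumptions, because the protocol gives no values.** Baseline-to-follow-up correlation r from 0.4 to 0.9; ratio k of follow-up SD to baseline SD from 0.9 to 1.1; SD of a calendar-driven shift in symptoms from 0 to 0.3 baseline SDs.

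**Step 1: correlation with no message effect.** Let B be the baseline score (SD 1), F the follow-up score (SD k), and D = B − F the reduction. Then cov(B, D) = 1 − rk and var(D) = 1 + k² − 2rk, so

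corr(B, D) = (1 − rk) / √(1 + k² − 2rk), which is √((1 − r)/2) when k = 1.

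For r = 0.7 and k = 1 this is √(0.3/2) = 0.387. For r = 0.9 and k = 1.1 it is (1 − 0.99)/√(1 + 1.21 − 1.98) = 0.01/√0.23 = 0.021.

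| r | k = 0.9 | k = 1.0 | k = 1.1 | simulated, k = 1.0 |
|---|---|---|---|---|
| 0.4 | 0.613 | 0.548 | 0.486 | not run |
| 0.5 | 0.577 | 0.500 | 0.427 | 0.496 |
| 0.6 | 0.538 | 0.447 | 0.360 | 0.450 |
| 0.7 | 0.499 | 0.387 | 0.281 | 0.391 |
| 0.8 | 0.460 | 0.316 | 0.179 | 0.320 |
| 0.9 | 0.436 | 0.224 | 0.021 | not run |

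The last column is a 10-fold cross-validated correlation from a linear model with n = 20,000, zero mean change, no message effect, and five uninformative features beside the baseline score. The same uninformative features, used alone against baseline-adjusted change, gave correlations between −0.010 and 0.014. The apparent performance therefore comes from the baseline score.

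**Step 2: how convincing this would look.** The null standard error of a correlation is about 1/√(n − 3): 0.022 at n = 2,000, 0.007 at 20,000 and 0.004 at 60,000. A value of 0.39 would be far outside chance at any of these sizes.

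**Step 3: does the measure register a benefit?** Adding the same 0.25 SD improvement to everyone left the simulated correlation at 0.391 (r = 0.7). The measure does not respond to a uniform benefit, so it says nothing about the average size of the reduction.

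**Step 4: the 6-week calendar variable.** At r = 0.7, still with no message effect:

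| SD of calendar shift | without the variable | with it |
|---|---|---|
| 0 | 0.391 | 0.391 |
| 0.1 | 0.390 | 0.409 |
| 0.2 | 0.374 | 0.448 |
| 0.3 | 0.366 | 0.509 |

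The variable adds nothing if symptoms do not move with the calendar, and it adds more the more they do.

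**Step 5: would changing the target be enough?** In a least-squares model that includes B, the predicted change is B minus the predicted follow-up score, so the residuals differ only in sign and the RMSE is identical. With baseline as the only informative feature, the correlation between predicted and observed follow-up score is r itself: 0.5, 0.6 and 0.7, against 0.50, 0.45 and 0.39 for change. The score is equal or higher. What removes the artefact is subtracting what the baseline score already explains. In R² terms at k = 1 that is (1 − r)/2 = 0.25, 0.20 and 0.15 of the variance of change, all of which belongs to a baseline-only benchmark.

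**The case against.** The strongest reply is that this analysis is exploratory. The Results section adds it to the conventional statistics to look for data-driven patterns, and neither the outcome list nor the hypotheses mention it. That stands, and it limits the point to the prediction claims.

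It can also be said that the target is defined operationally as change in scores, that the protocol nowhere says a good correlation would show the messages worked, and that the missing control arm is disclosed. All true. But the disclosure is tied to hypothesis 3, and the prediction target still carries the name efficacy with no benchmark beside it.

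The features are not itemised, and r and k are unknown, so a reader who concludes that a sizeable correlation is guaranteed goes too far. It is probable over most of the plausible range and vanishes at one corner of it.

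On the pandemic data, the protocol presents them as adjustment and does not say outright that they enter the same model as the baseline features. They are external series, not leaked outcomes. What remains is that the two descriptions of the machine learning inputs do not match.

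Two further readings are tempting but unsupported. Because everyone surveyed on one date shares the same pandemic values, a reader might infer that the assurance "the data being tested has never been seen in any way by the model" is false. That sentence is about held-out records, and a shared calendar covariate does not reveal a held-out subscriber's outcome. Random folds validly estimate performance for new subscribers from the same period. A reader might also infer that Pearson correlation is itself an error. It is a legitimate measure of discrimination, and nothing in the protocol suggests that miscalibration is likely between folds drawn from one population.

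**Conclusion.** The point holds as a should-fix item on the secondary prediction analysis. With no message effect, the planned score would probably be clearly above zero: 0.55 down to 0.22 for r from 0.4 to 0.9 at equal SDs, higher if follow-up scores are less variable, and close to zero (0.02) only at r = 0.9 with a follow-up SD 10% larger. These figures rest on assumed r and k and on the baseline scale scores being among the features, which is the natural reading of the Methods and Results sections together. The simulation used a linear model with one level of cross-validation, not the planned algorithms with nested selection; nesting would not remove an association that exists in the population.

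The calendar component is weaker. It raises the score only if symptoms track the pandemic, and its size depends on an assumed shift of up to 0.3 SD. The mismatch between baseline features and 6- and 12-week inputs is in the text whatever that size.

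A reader might infer that the evaluation of hypothesis 3 is compromised as well. The documents do not support that: the within-subject tests of change are separate and unaffected by how the prediction models are scored.

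**What to change.** 1. Make the main performance measure the gain in out-of-sample R², with RMSE or MAE, over a benchmark containing only that scale's baseline score. Where calendar variables are used, put them in the benchmark too. The correlation may stay as a supplementary figure. Switching the target to the follow-up score is acceptable but not sufficient on its own.
2. Report the baseline-feature model without the 6- and 12-week pandemic and economic variables, and keep those variables in a separate model described as explanatory.
3. Replace efficacy, as the name of the prediction target, with change (or outcome) at 6 and 12 weeks, and state that without a control arm the models do not predict treatment effect. This is needed even if the gain over the benchmark is positive.

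Calibration measures and folds blocked by date are optional additions; blocked folds would show performance on dates outside the training data, which is a different question.

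The cost is analysis code and wording, with no new data and no change to the primary tests. The drawback is that performance over the benchmark will look less impressive than the raw correlation.
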